## Abstract

**Background:**

Music therapy has been shown to be effective for multiple clinical endpoints associated with substance use disorder such as craving reduction, emotion regulation, depression, and anxiety, but there are a lack of studies investigating those effects in UK Community Substance Misuse Treatment Services (CSMTSs). Furthermore, there is a demand for identifying music therapy mechanisms of change and related brain processes for substance use disorder treatment. The present study aims to evaluate the feasibility and acceptability of music therapy and a pre-test, post-test, and in-session measurement battery in a CSMTS.

**Methods:**

Fifteen participants, from a community service based in London, will take part in a mixed-methods non-blind randomized-controlled trial. Ten participants will receive six-weekly sessions of music therapy in addition to the standard treatment offered by the CSMTS—five of them will receive individual music therapy and five of them will receive group music therapy—while a further five participants will act as a control group receiving standard treatment only.

Satisfaction and acceptability will be evaluated in focus groups with service users and staff members following the final treatment session. Moreover, attendance and completion rates will be monitored throughout the intervention. Subjective and behavioral indexes will be assessed before and after the interventions to explore the effects of music therapy on craving, substance use, symptoms of depression and anxiety, inhibitory control, and will be correlated with associated neurophysiological signatures. In-session analysis of two individual music therapy sessions will serve to explore how music and emotion are processed in the brain within the therapy. The data collected at each step will be included in an intention-to-treat analysis basis.

**Discussion:**

This study will provide a first report on the feasibility of music therapy as an intervention for participants with substance use disorder engaged within a community service. It will also provide valuable information regarding the implementation of a multifaceted methodology that includes neurophysiological, questionnaire-based, and behavioral assessments in this cohort. Notwithstanding the limitation of a small sample size, the present study will provide novel preliminary data regarding neurophysiological outcomes in participants with substance use disorder that received music therapy.

*Trial Registration:* ClinicalTrails.gov, NCT0518061, Registered 6 January 2022, https://clinicaltrials.gov/ct2/show/NCT05180617

## Background

It is estimated that over 5% of the United Kingdom population suffers from Substance Use Disorder (SUD) which is directly (i.e., substance overdoses) or indirectly (i.e., substance use as a risk factor for premature death) considered responsible for over 4,000 deaths each year [1]. Among the people who accessed support with substances via adult drug and alcohol services from the National Health Service (NHS) and non-NHS providers in the UK between 2019 and 2020, only 3% of them received treatment in an inpatient setting and 2% of them in a residential setting [2], with numbers declining further for the period 2020 and 2021 (i.e., only 3% received treatment in an inpatient setting and 1% in a residential setting) [3]. In contrast, Community Substance Misuse Treatment Services (CSMTSs), inpatient detoxification, residential rehabilitation or private counseling see a much larger number of clients across the country. The generalization and application of the evidence base of Music therapy treatment [4], which is largely based on inpatient settings, remains challenging.

Despite the growing interest in using music therapy (MT) in SUD treatment [5–7], there is similarly a marked absence of studies that include participants from CSMTSs, forming a gap in the literature that needs to be addressed [4, 6, 7]. The current protocol aims at outlining the steps for covering this gap.

SUD has been defined as a chronic, and often relapsing disorder [8–10] targeting multiple interacting neural circuits in the brain [8, 9, 11] and associated with a cluster of cognitive, physiological, and behavioral symptoms indicating that the individual continues to use the substance despite adverse consequences such as craving, anxiety and depressive symptoms [12]. Research on the neuroscience of music showed that processing of pleasing musical stimuli is associated with overlapping patterns of neural activations induced by euphoretic psychoactive drugs [13, 14], suggesting how MT may modulate dopaminergic-dependent neural circuits and work on emotional reactions. This might help clients to overcome the compulsive characteristics of this condition and its state-dependent memories [15]. A recent Cochrane systematic review identified MT as a valuable SUD add-on treatment to standard care [4]. MT is defined as a clinical intervention delivered by an accredited music therapist adopting music and its elements as a therapeutic tool to accomplish individualized goals within a therapeutic alliance and facilitate positive changes in clients’ emotion regulation, motivation, and social engagement [4, 16–18]. The physiological effects of MT can be examined non-invasively through neuroscience methods, such as electroencephalography (EEG) to measure brain activity [19, 20]. Throughout MT sessions, important moments that represent personal changes accompanied by shared emotions and mutual understanding, can be identified [21, 22]. Recent research suggested that during moments of therapeutic interest (e.g., emotionally relevant moments) there exists increased synchronization of brain activity between the music therapist and the participant [22]. These moments can be further examined through hyperscanning technology [23, 24] allowing for the simultaneous recording of the brain activity of both the music therapist and the participant [21, 22]. Combining EEG-hyperscanning with audio–video (AV) recording of therapy sessions represents an innovative approach to tracking the temporal dynamics of event-related peaks related to emotional processing during therapy. The analysis of these data would build on the existing research regarding interacting brain synchronization [22, 24] and further improve our understanding of brain activity during possible emotionally challenging moments in the therapy, such as the experience of a craving state.

Craving is considered a key symptom for SUD, maintaining the pathological vicious circle of this condition [11, 25] and manifesting itself as an “intense desire or urge for the drug” [12]. Furthermore, anxiety and depression are two common conditions in individuals using substances [12] and MT has shown efficacy in reducing depressive [16, 17] and anxiety symptoms [16, 18] in individuals not suffering from SUD. Studies including SUD populations suggested that mental health clinical endpoints improved in those participants after receiving MT: beneficial effects have been pointed out for depressive symptoms [26, 27], anxiety symptoms [26, 28, 29], negative emotions (i.e., anger) [26] and craving [30–32]. The importance of measuring mental health indexes in MT settings for SUD and assessing brain data to explore the underlying mechanisms of a potential music-therapeutic success have been recently emphasized [4]. The reduction of craving, depression and anxiety are primary outcomes for participants receiving MT in addition to standard care, when compared to participants receiving standard care alone; especially if the MT intervention lasted from 1 to 3 months [4]. However, despite empirical evidence suggesting that MT is effective for SUD individuals, outcomes from studies using heterogeneous methodologies and MT intervention types are not always consistent [6]. Likewise, despite reported improvements in several mental health clinical endpoints, the mechanism of therapeutic change underlying the effects of MT for these variables is yet to be identified [4] and future randomized control trials adopting neuroscience research methods may provide insights not only on the efficacy of MT on relevant symptoms associated with SUD (e.g., depression, anxiety and craving) but also on the pre-post MT changes in brain activity that is hypothesized to underpin those conditions.

A recent Cochrane systematic review recommends that research on MT for SUD individuals should (I) include a broader diversity of treatment settings while decreasing heterogeneity within and between studies, (II) consider the associations between mental health and SUD, (III) evaluate the impact of length of treatment, (IV) assess outcomes at medium- and long-term follow-up, (V) match MT intervention to the phase of SUD treatment, and (VI) determine mechanisms of therapeutic change [4]. The study reported here will address some of those recommendations (diversity, mental health, treatment length) to determine the feasibility of implementing MT as an intervention for participants with SUD that are engaged within CSMTSs, a hitherto underrepresented cohort. In addition, the present study will test the feasibility of applying a pretest, posttest, and in-session measurement battery within a CSMTS to explore the efficacy and underlying mechanisms of MT change. Indeed, the novel nature of the current research project is the analysis of mechanisms of therapeutic change from two angles: (I) through the combination of subjective self-report measurements and objective EEG assessment comparing pre/post intervention changes and (II) through the study of MT session delivery and creative process analysis. The latter will also be supported by utilizing Electronic Music Production Instruments (EMPI) during therapy. EMPIs provide significant benefits to the analysis of musical interactions through incorporated multi-track recording functionality, enabling the separation of participant and therapist instrument play and affording detailed analysis of the musical mechanisms at work [33]. Thus, the project has the potential to identify an intervention that may enhance the mental wellbeing and recovery journey for individuals experiencing SUD and enhance the care offered by CSMTSs in the long term.

## Methods

### Study aims and specific objectives

The main aim of this study is to test the feasibility of implementing individual music therapy (IMT) and group music therapy (GMT) as an intervention for service users (SUs) experiencing symptoms of depression and/or anxiety and engaged with CSMTSs. In order to approach the primary aim, our objectives are (I) to measure qualitative data on SU satisfaction with the MT program, (II) to measure retention in treatment and (III) to collect their feedback over the course of the treatment. The secondary aims of this project are to examine the feasibility of applying a pre-test, posttest, and in-session assessment battery as well as to measure the effects of MT (GMT and IMT) on mental health and the neural processing associated with it. We aim to explore the effects of MT in addition to standard treatment (ST) versus standard treatment alone. Further secondary aims concern the exploration of features of the therapeutic relationship and the role of music technology in the delivery, recording, and analysis of music therapy sessions. In order to approach the secondary aims, our objectives are: (I) To measure the effects of MT in addition to ST on the following treatment outcomes in comparison to ST alone: (a) substance use, (b) physical, mental wellbeing and quality of life, (c) retention in treatment, (d) engagement with treatment, (e) completion rate, (f) emotional processing, (g) psychological symptomatology. (II) To measure reduction in craving intensity after single MT sessions. (III) To compare the effect of MT in addition to ST versus ST alone on craving, inhibitory control, depression, anxiety and the respective associated neural signatures. (IV) To explore the perceived therapeutic alliance in IMT sessions. (V) To explore the neural dynamics of emotional processing during IMT sessions. (VI) To explore SU experiences of using music technology in an MT intervention. (VII) To explore how music technology can be utilized in the subsequent analysis of audio data of musical interaction recorded during MT sessions.

We expect that an MT intervention, carried out alongside the ST, will (a) be feasible and acceptable for individuals receiving community-based substance misuse treatment; (b) lead to a decrease in the symptoms of anxiety, depression and craving that correlates with changes in the underlying neural processes; (c) improve treatment outcomes for SU in CSMTSs; (d) improve inhibitory control that correlates with a change in the underlying neural process and, potentially, with changes in the craving intensity.

### Study design

Westminster Drug Project (WDP) is a substance misuse service provider delivering services within the UK. WDP’s Innovation & Research Unit (IRU) and the Cambridge Institute for Music Therapy Research (CIMTR), Anglia Ruskin University, have designed a mixed-methods feasibility study to address these aims and objectives. The study is designed as a three-armed study (Fig. 1) with group 1 receiving 6 weekly sessions of GMT alongside ST (see section “interventions”), group 2 receiving 6 weekly sessions of IMT alongside ST, and group 3 serving as a control group (CG), receiving 6 weeks of ST only. All participants will take part in pretest–posttest assessment (i.e., baseline and post-intervention measures) including subjective (i.e., multi-item questionnaires), behavioral (i.e., Go/No-Go task) and EEG measurements to assess several mental-health-related clinical endpoints. SUs allocated to group 2 will receive IMT while simultaneously EEG-hyperscanning is being recorded during the 2^nd^ and 5^th^ therapy sessions. After these two sessions, participants will undergo a semi-structured interview to select moments of therapeutic interest and complete a multi-item questionnaire measuring the quality of therapeutic relationship. Each participant allocated to GMT and IMT will also complete a single-item questionnaire to assess the intensity level of craving. Feedback from participants will be collected throughout the study and, where possible, requests will be implemented into the subsequent session. Engagement and treatment status of participants will be assessed 6 months post-intervention. After the intervention two different focus groups will be conducted: one involving MT participants and another involving a Staff Group (SG) of 4–8 WDP staff members who work with the service users involved. The SG focus group will explore the feasibility of MT from several perspectives, including those involved in the set-up of the MT sessions. Whilst the duration of the entire study is outlined to be a period of 3 months, participants will be committed for 8 weeks.

**Fig. 1 Fig1:**
[figure not shown]
Consort flowchart representing study design and procedure

### Patient and public involvement

The research team attended a SU consultation, organized by WDP, to present the project design and gather feedback from a SU perspective. A total of 7 SUs attended this consultation. The aim of this consultation was to get initial views of the design, participant time commitment, general interest in music therapy and thoughts on the EEG element. The research team received positive feedback from the SU's in attendance. The consultation also provided some input into the music therapy sessions, with suggestions on which instruments should be available. Further to this consultation, the research team will hold drop-in session within the WDP service during the recruitment window. This drop-in session will seek to aid recruitment and provide further information about the project and what participation will involve. Interested service users will also be able to ask the research team questions regarding the study and offer feedback.

### Participants

Fifteen SUs and, from a minimum of 4 to a maximum of 8 staff members, will be recruited from WDP. In total, we will recruit between 19 and 23 participants. The inclusion criteria for the recruitment of SUs include: (I) being a SU in structured treatment for drug and/or alcohol misuse, (II) being 18 years old or older, (III) reporting symptoms of depression and/or anxiety, (IV) being deemed suitable to take part in a group/individual setting by their key workers (who are Recovery Practitioners responsible for coordinating and delivering psychosocial interventions for SUs), (V) being right-handed.

The exclusion criteria for the recruitment of SUs include: (I) having a legal requirement to attend as part of a Drug Rehabilitation Requirement or Alcohol Treatment Requirement as this may impact engagement results, (II) being unable to provide informed consent due to a lack of mental capacity, (III) little/no understanding of spoken English as all sessions will be carried out in English and instructions for subjective measures used in this project are in English, (IV) being left- and mixed-handed: an outcome measure utilized (i.e., the EEG frontal alpha asymmetry) is modulated by handedness direction (i.e., left-handed, right-handed) providing empirical justification for the practice of excluding left-handers and mixed-handers when exploring relationships between this neural marker and other variables [34], (V) not being registered with a general practitioner (GP)/unable to provide GP details: we will require GP details to notify them in case of any incidental EEG findings. Furthermore, participants who disclose in the consent form that they had experienced a Stroke, Traumatic Brain Injury, or Epilepsy will be contacted by the research team to discuss if they can wear an EEG cap and participate in the measurements. Our inclusion and exclusion crit﻿eria are broadly based on the eligibility criteria for SUs to attend most groups in the service. We expect participants to either be abstinent or present with low to moderate substance use. Participants would also likely be housed and have access to public funds. While this presents a sample with diverse substance use patterns and individual circumstances, this is more representative of the cohort that would use this type of intervention. The diversity in participants may aid determining feasibility and acceptability of the intervention and provide value in planning further more focused studies. Regarding SG, only members of WDP staff will be included in this group.

### Recruitment

Opportunistic sampling will be used, with eligible SUs being identified and then provided an information sheet detailing the project. The service will also feature a poster advertising the project and asking interested SUs to contact WDP staff for more information. SUs volunteering to participate will be asked to complete an informed consent form. Once participants are recruited the researchers will randomly assign participants to one of the three groups (GMT, IMT or CG).

Recruitment will be carried out by advertising the project in the community and by WDP staff identifying eligible SUs through WDP's case management system. SUs can choose to opt out from being approached about research, so only those who have indicated that they are happy to be approached about research will be contacted. For those that have not been identified through the case management system but approached by their key worker, the key worker or service administrator will ascertain eligibility through the case management system and in keywork sessions. SUs identified as eligible will be provided with the information sheets and consent forms and asked to return these. Consent will be taken with a member of the research team or WDP staff present. This is to ensure that someone is there to help with questions and understanding. The long version of the participant information sheet is a comprehensive document including information on the project, ethical information, benefits, and potential risks of participating in the study. The short version of the participant information sheet includes a brief overview of the project and what participating in the study entails.

The staff cohort will be recruited by directly approaching staff members who were involved in the project or may be involved in future forms of the program. This will be done by emailing them directly or attending staff meetings and asking for volunteers to participate. Staff members will also be invited to attend the drop-in session. SUs who participate will be rewarded Capital Card^®^ points. Points will be awarded for each session completed, including the focus group and interview. WDP Capital Card^®^ is a reward card scheme to help SUs with their recovery journey ([35]; https://www.wdp.org.uk/the-capital-card). Where the project has issues recruiting the full number of 15 SU participants, we will extend the recruitment window to 2–3 months and we will re-run the drop-in session to attract more SUs. We will also contact WDP key workers to promote the study. Recruitment for GMT will continue until 5 participants are recruited and allocated to this group. If the 5 participants are not recruited within 2 months, the GMT sessions will start once at least 3 participants have been allocated. The GMT will continue while 3 participants remain in the study. The start of the IMT sessions will be staggered: SUs allocated to the IMT group will start their MT sessions within 1–2 weeks of being allocated to this group. If a participant in the IMT group drops out within the first 2 weeks, we will re-recruit and the new participant will start from week 1. We will only re-recruit twice before continuing with the remaining IMT participants. If after 3 months, the project does not have enough participants to go ahead, the research team will discuss additional recruitment strategies, widening the inclusion/exclusion criteria or a possible change in study location. The research team will take any feedback from SUs or staff around recruitment and incorporate where necessary. Where a participant decides to withdraw from the study, they will be provided an exit survey and withdrawal confirmation form. This form gives the participant the option to decide if the data collected up to their withdrawal will be kept and used in the final analysis or destroyed and not used in the final analysis. If they choose not to complete this survey or ask that all their data collected up to their withdrawal is deleted, the exit survey will be destroyed.

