### Analysis strategy regarding the main study aim

Data analysis of the main study aim will be performed by comparing feasibility-related measures collected at the end of the treatment between participants allocated to the IMT or GMT groups. Descriptive statistics will be used to examine the rate of acceptability and satisfaction in these two experimental groups. Primary outcome measures (feasibility-related measures) that will be used are: (I) retention in treatment, which will be assessed by collecting attendance sheets and treatment status. The treatment status from participants receiving IMT, GMT and ST will be collected by WDP’s case management system 1-month post-intervention. This will provide information about retention in treatment, treatment engagement and completion rate. (II) Acceptability of treatment, which will be assessed by collecting a participant satisfaction survey as a post-intervention measure (at week 8) and implementing two post-intervention focus groups (FG1 and FG2) (at week 9). Primary outcome measures will only be administered/conducted after the end of the intervention with the aim of collecting the subjective perspective of the participants and staff involved in focus groups and will be subjected to thematic analysis using a specific thematic analysis model [57]. From this data themes will be identified pertaining (I) to participants' experience of MT in a CSMTS and (II) to participants’ experience of using music technology in music therapy.

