### Sample size and dosage

Secondary purposes will be investigated within the frames of a feasibility study that include, as a corollary, the recruitment of a relatively small sample size to have preliminary data to determine whether interventions and research procedures are appropriate, acceptable, and practical [61].

Therefore, conclusions regarding mental health clinical endpoints as well as the therapeutic relationship and the role of music technology will be interpreted with care and presented as preliminary. Presently, positive results regarding the effectiveness of MT, as compared to a ST provided by the community, reflecting an improvement in the mental health of SUD participants have not been reported yet; for this reason, notwithstanding the small sample size limitation, it is essential to fill this gap in the literature. Additionally, analysis of the primary and secondary study aims will be performed on an intention-to-treat basis to manage drop-outs and missing data. A total of 6 IMT and GMT sessions will be offered. Patients with fewer sessions will not be excluded from data analysis (intention-to-treat principle; [62]). Nevertheless, to minimize missing data imputation, for participants not attending the post-treatment test battery at week 8, the last observation carried forward (i.e., in this case, baseline measurements at week 1) will be used.

Whilst depressive [26, 27], anxiety [26, 28, 29] and craving [30–32] symptoms have been shown to improve after MT in individuals with SUD, this will be a first attempt to study these dimensions in a community setting by measuring their neural correlates.

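### Early drop-outs are replaced in the IMT arm only, and the article conflicts on whether the person replaced still counts in the IMT-versus-GMT retention comparison

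*Protocol article*

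**What the plan says.** All references are to the protocol article.

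- **Allocation.** The abstract plans fifteen service users, of whom "five of them will receive individual music therapy and five of them will receive group music therapy", with five controls. The Recruitment section has recruited participants randomly assigned among the three groups.
- **Replacement in IMT.** Recruitment: "If a participant in the IMT group drops out within the first 2 weeks, we will re-recruit". The newcomer begins at week 1. The limit is: "We will only re-recruit twice before continuing with the remaining IMT participants".
- **GMT and control.** Recruitment fills GMT before it starts, allows a start with three people after two months, and lets the group run on while three remain. No one who leaves after the start is replaced. Control has no replacement rule.
- **Primary analysis.** The main-aim analysis works by "comparing feasibility-related measures collected at the end of the treatment between participants allocated to the IMT or GMT groups". Retention, taken from attendance sheets and treatment status, is the first measure listed there.
- **Who is analysed.** Sample size and dosage states that "analysis of the primary and secondary study aims will be performed on an intention-to-treat basis", and that having fewer sessions is no ground for exclusion. The secondary-aims analysis section says that people who disengage contribute their measures if they attended more than two sessions.

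**The concern.** Leaving IMT in the first two weeks is a primary-outcome event. Under the replacement rule the vacated place can be refilled; the same event in GMT leaves a visible gap. If the five IMT places become the denominator, IMT looks better retained than GMT even when the true drop-out is identical.

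The window also covers IMT's heavier attendance. The Procedure section puts the visit at about 115 minutes in weeks 2 and 5, against 60 minutes otherwise, because of the EEG preparation and the interview. Losses caused by that burden, which a feasibility study wants to see, are among those that can be replaced.

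There is a second effect. A person recruited to fill an IMT vacancy has an arm set by the vacancy. If two such people are analysed among ten music therapy participants, 2 of 10 in the comparison of music therapy with standard treatment alone were not randomised. The Discussion and Conclusion say that the study should inform a larger trial, so a distorted retention figure could affect its choice of format and its drop-out allowance.

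**Working it through.** **1. The plan's own figure.** 5 + 5 + 5 = 15 service users, as stated. With two replacements, up to 5 + 2 = 7 people could enter IMT, yet the article keeps describing that arm as five.

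**2. The inclusion rules side by side.** Sessions are weekly, so a person who leaves in the first two weeks has normally attended at most about two. Such a person cannot meet the more-than-two-sessions condition in the secondary-aims section. The intention-to-treat statement in Sample size and dosage, which covers primary and secondary aims, keeps the same person in. The two rules give opposite answers for exactly the people whom the IMT rule replaces.

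**3. Fixed examples** (replacements stay, no later loss):

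| Early losses in each arm | IMT, five places | IMT, all ever allocated | IMT, originally randomised | GMT |
|---|---|---|---|---|
| 1 | 5/5 = 100% | 5/6 = 83% | 4/5 = 80% | 4/5 = 80% |
| 2 | 5/5 = 100% | 5/7 = 71% | 3/5 = 60% | 3/5 = 60% |

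**4. Expected values.** Inputs: five places per arm; at most two IMT replacements (re-recruiting twice is read as two persons); the same early drop-out risk q for everyone, replacements included; no later loss. The values of q are assumptions, since the article gives no rate.

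Let L be the number of early losses among seven possible IMT entrants, binomial (7, q). All five places are filled if L is 2 or less; otherwise 7 − L are filled. The expected proportion filled is therefore

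[5 − Σ (k − 2) P(L = k), summed over k = 3 to 7] / 5.

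For q = 0.3 the sum is 0.512, so (5 − 0.512)/5 = 0.898. GMT, without replacement, is 1 − q = 0.700.

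| q (assumed) | IMT, five places | GMT | Gap (points) | IMT, all ever allocated | Gap (points) |
|---|---|---|---|---|---|
| 10% | 99.4% | 90.0% | 9.4 | 91.4% | 1.4 |
| 20% | 96.3% | 80.0% | 16.3 | 82.0% | 2.0 |
| 30% | 89.8% | 70.0% | 19.8 | 71.9% | 1.9 |
| 40% | 80.3% | 60.0% | 20.3 | 61.4% | 1.4 |

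If only those originally randomised are counted, IMT also has expectation 1 − q and the gap is zero. With a further 20% late loss in both arms, the gap on the five-places reading is 7.5, 13, 16 and 16 points.

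**5. Chance of no visible early loss at q = 30%.** IMT: 0.7^5 × (1 + 5 × 0.3 + 15 × 0.09) = 0.168 × 3.85 = 65%. GMT: 0.7^5 = 17%.

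**The case against.** A reader might infer that the rule breaks randomisation, hides IMT attrition and violates intention-to-treat. The article does not support that as a statement of fact.

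- **Hidden attrition.** Nowhere does the article say that a replaced person leaves the denominator. The main-aim analysis speaks of participants allocated to an arm, and an early leaver was allocated. Table 1 lists attendance sheets and the exit questionnaire under the primary outcome, so early departure is itself recorded. This stands and makes the distortion conditional. The protection is incomplete, however: the Recruitment section lets people who withdraw have their data and exit survey destroyed, and the more-than-two-sessions rule points the other way, although it sits in the secondary-aims section.
- **Intention-to-treat.** Adding a person does not breach the principle if everyone allocated is analysed. This stands.
- **Randomisation.** The article does not say how a re-recruited person is allocated. Direct entry to IMT is the natural reading of starting at week 1 after an IMT vacancy, but it is an inference.
- **Practical reason.** IMT starts are staggered, so a newcomer can begin at week 1; GMT starts as one group and cannot easily admit one. This explains the asymmetry and rules out simply extending replacement to GMT. It does not settle how replaced people are counted.
- **Consequence.** The primary comparison is descriptive, no progression threshold is stated, and the secondary results will be presented as preliminary. This stands and limits the severity. How replaced people are counted might also be left to a fuller document, but here the article itself states two rules that disagree.

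**Conclusion.** The point holds in conditional form and is a should-fix. Replacement in IMT alone is stated outright, and so is the use of retention as a primary measure compared between IMT and GMT. What is unsettled is the denominator, because two inclusion rules disagree about early leavers.

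If places are counted, equal true drop-out of 20% to 40% would show as an advantage of about 16 to 20 points for IMT. If everyone ever allocated is counted, the difference is about 2 points at most. These sizes rest on assumed drop-out rates, the same risk for replacements, and at most two replacement persons; re-recruiting twice could instead mean two rounds. No type I error or power is at stake. That randomisation is broken, or that attrition is certainly concealed, goes further than the text allows.

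**What to change.** 1. State that every originally randomised participant, including an early leaver who is replaced, stays in the retention denominator and in the intention-to-treat comparisons.
2. Reconcile the more-than-two-sessions rule in the secondary-aims section with the intention-to-treat statement in Sample size and dosage, so that one rule governs early leavers.
3. State how replacements are allocated. If they enter IMT without randomisation, use them only for the in-session EEG, HAQ-II and interview data, report them separately, and leave them out of the IMT-GMT comparison and the comparison of music therapy with standard treatment alone. If late entrants are to count in those comparisons, randomise them among the arms with open places.
4. Say whether re-recruiting twice means two persons or two rounds.

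The cost is wording, a slightly less favourable reported IMT retention, and up to two fewer people in the IMT comparison. Replacement can continue for its practical purpose of supplying in-session data, and GMT needs no replacement rule.
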